### Analysis

Reporting will be according to CONSORT criteria. Analyses will follow the intention-to-treat principle. Missing data will be treated using multiple imputation, as recommended for people with dementia. [55]

#### Primary objective

Mixed effects linear regression will be used to analyze differences in the primary outcome (percent achievement of physical activity recommendations) as a function of group (CB, HB), time (baseline, follow-up and interim month 1, month 2 where relevant), and group x time. A random effect for participants and site (CB) will be included in the models.

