## Methods & design

This is a pragmatic, randomized, parallel group trial to explore the relative effectiveness of two exercise delivery options (CB versus HB) among 60 people with MCI and mild dementia. The study will be conducted at two sites in Canada: Toronto (Sunnybrook Health Sciences Centre and University Health Network-Toronto Rehabilitation Institute) and Kitchener-Waterloo (University of Waterloo). Enrollment of participants began in September 2016 and is expected to continue until September 2018.

The study flow is shown in Fig. 1. Assessments will occur at baseline and immediately after the completion of the intervention. In addition to these assessments, physical activity, health status, and health care utilization will be reported monthly. Participants will be randomly assigned to CB or HB after baseline assessments, blocked by site, via a central internet randomization service (www.randomization.com). The randomization will be managed by a department research assistant not involved in the assessments and communicated to the participants directly or via the site research coordinator. Those who assess and those who analyze outcomes will remain blinded to allocation throughout and will report whether there was any indication of group allocation. In addition, analyses will be done by code (that is, Group ‘A’ and ‘B’) with code only revealed after analyses are complete. Due to the nature of the intervention, participants and exercise physiologists will not be blinded to group but participants will be blinded to the study hypotheses.

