### Measures

All participants will be assessed at the center at baseline and after the intervention. Participants will also complete a telephone assessment 1 month and 2 months into the program. Measures by time points are listed in Table 1. Assessors are blinded to group allocation throughout the study. Any possible disclosure will be noted.

**Table 1 Tab1:** Assessments by time point

	Baseline	1-month	2-month	Post-intervention
Participant Descriptors				
Participant information questionnaire	X			X
Height, weight, waist, BP	X			X
Medications	X			X
Physical activity history	X			
Social Support for exercise survey	X			X
BBAQ	X			X
Self-reported health	X	X	X	X
Falls	X	X	X	X
Secondary & Tertiary Outcomes				
RUD-Lite	X	X	X	X
PASE	X	X	X	X
ADAS-Cog	X			X
Stroop Test	X			X
Trails Making Task	X			X
Semantic Fluency	X			X
SPPB	X			X
DAD-6	X			X
EQ-5D	X			X
NPI-Q	X			X
6 min walk	X			X
25 ft. single & dual task	X			X
GAS	X			X
Primary Outcome				
Actigraph	1-week following			1-week following

*BP* blood pressure, *BBAQ* Barriers to Being Active Questionnaire, *RUD-Lite* Resource Utilization Dementia-Lite questionnaire, *PASE* Physical Activity Scale for the Elderly, *ADAS-Cog* Alzheimer Disease Assessment Scale-cognitive, *SPPB* Short Physical Performance Battery, *DAD-6* 6-item Disability Assessment for Dementia scale, *EQ-5D* Euro-Qol 5D, *NPI-Q* Neuropsychological Inventory, *GAS* Goal Attainment Scaling

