#### Primary outcome

The primary outcome will be achievement of aerobic activity guidelines for older adults (percent of 150 min/week of moderate physical activity) as measured using an activity monitor (Actigraph GTX3+), [29] which contains an accelerometer that is validated for measurement of physical activity by intensity among older adults. [30, 31]. Participants will wear the activity monitor for one week following the baseline assessment, with the expectation that at least 5 days of usable data will be achieved as is required for reliable estimates of habitual physical activity. [32] Wear time will be validated by established parameters. [33] We will determine time spent in moderate or vigorous physical activity using cut-offs based on recent studies of older adults (≥810 cpm). [35] The time spent in moderate or vigorous activity will be divided by the recommendation (150 min/week or 21.4 min/day) to get percent achievement of the guidelines.

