### Sample size calculation

Sample size is based on the primary objective, to detect a significant difference in percent achievement of physical activity recommendations (continuous variable) between CB and HB groups over the intervention period. A recent Cochrane review of CB versus HB among older adults indicated that HB exercise had better physical activity achievement than CB, with an effect size of 0.8. [27] There were no studies that targeted people with cognitive impairment. To account for the possibility that cognitive impairment may reduce the feasibility of HB, we used a smaller effect size of 0.6, an alpha of 0.05 and a beta of 0.85 with two-group repeated measures MANOVA (within and between factors) to estimate a sample size of 39. We assumed 35% drop out, similar to our pilot work and to a previous study of exercise in people with MCI, [54] to bring the required sample size to 60.

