#### Tertiary objective

Change in each tertiary outcomes between T1 and T2 will be examined using mixed effects linear regression as a function of group, time, and group x time interaction. A random effect for participants and site will be included in the models.

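### The primary model compares changes from baseline without adjusting for baseline; this is valid but less precise than a baseline-adjusted contrast from the same two Actigraph weeks

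*Protocol article*

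**What the plan says.** The primary outcome is continuous (Protocol article, *Primary outcome*): "percent of 150 min/week of moderate physical activity) as measured using an activity monitor". Under *Primary objective* it is analysed by mixed effects linear regression "as a function of group (CB, HB), time (baseline, follow-up and interim month 1, month 2 where relevant), and group x time". The same paragraph adds: "A random effect for participants and site (CB) will be included in the models". No baseline covariate and no common baseline mean are mentioned, and none of the three terms is named as the primary contrast. *Tertiary objective* repeats the structure: "mixed effects linear regression as a function of group, time, and group x time interaction".

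In Table 1 (*Measures*) the Actigraph row reads "1-week following" in the baseline and post-intervention columns and is empty at months 1 and 2. The interim contacts are by telephone: "Participants will also complete a telephone assessment 1 month and 2 months into the program". The interim levels of time therefore do not apply to the primary outcome, which has two measurements per participant.

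On the order of events, *Methods & design* says: "Participants will be randomly assigned to CB or HB after baseline assessments, blocked by site". *Primary outcome* puts the first monitoring week after the baseline assessment.

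**The concern.** A model with a separate group term lets each arm have its own baseline mean. Group by time then subtracts the whole observed baseline difference from the follow-up difference. In a randomised trial the baseline means are equal in expectation, so any observed difference is chance. Part of it carries over to follow-up and should be removed, but only in proportion to the slope of follow-up on baseline. Subtracting all of it adds noise when that slope is below 1.

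Precision is at stake, not validity. The trial plans on 60 randomised and about 39 completing. At that size a chance baseline difference can be appreciable, and the baseline measurement that would sharpen the comparison is already being collected.

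**Working it through.** **Inputs.** From *Sample size calculation*: "we used a smaller effect size of 0.6, an alpha of 0.05 and a beta of 0.85", repeated measures MANOVA, 39 participants, 35% dropout, 60 in total. From Table 1: two Actigraph weeks. Assumed, because the documents do not give them: the correlation ρ between the two weeks, and equal variances (relaxed in step 4). Results are in outcome-SD units.

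**Step 1: the plan's own figures.** With 0.85 read as power and 0.6 taken directly as the MANOVA effect size f(V), the within-between interaction test has λ = N × 0.6², df1 = m − 1 and df2 = N − 2 − (m − 1) + 1. With m = 4 time points this gives N = 39 (power 0.858). Then 39 / 0.65 = 60. The planned numbers reproduce, so n = 60 and c = 39 are used below, that is 30 and 19.5 per arm.

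**Step 2: complete pairs.**
- Planned contrast: per-person variance of a change = 2(1 − ρ).
- Baseline-adjusted: residual variance = 1 − ρ².
- Ratio = (1 − ρ²) / [2(1 − ρ)] = (1 + ρ)/2.
- SE = √(per-person variance × 2/19.5).

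| ρ | SE planned | SE adjusted | Variance ratio |
|---|---|---|---|
| 0.3 | 0.379 | 0.306 | 0.65 |
| 0.5 | 0.320 | 0.277 | 0.75 |
| 0.7 | 0.248 | 0.229 | 0.85 |
| 0.9 | 0.143 | 0.140 | 0.95 |

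Estimating the regression slope costs a factor of about 1 + 1/35 = 1.029 in variance at 39, so the first three ratios become 0.67, 0.77 and 0.87.

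A simulated trial of 39 complete pairs (ρ = 0.6) confirmed the identity. The random-intercept group by time estimate and the change-score comparison were both −0.2005 with SE 0.2435. On the same data the common-baseline mixed model gave SE 0.219 and the regression on baseline gave 0.205.

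**Step 3: with dropout.** Under the planned mixed model, participants with only a baseline week still inform the baseline means.
- Planned: variance = 2 × [(1 − ρ²)/19.5 + (1 − ρ)²/30].
- Common baseline mean: variance = 2 × (1 − ρ²)/19.5.
- Ratio = (1 + ρ) / [(1 + ρ) + 0.65(1 − ρ)].

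At ρ = 0.5, planned = 2 × (0.03846 + 0.00833) = 0.0936 (SE 0.306), constrained = 0.0769 (SE 0.277), and the ratio = 1.5/1.825 = 0.82.

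| ρ | SE planned | SE constrained | Variance ratio |
|---|---|---|---|
| 0.3 | 0.355 | 0.306 | 0.74 |
| 0.5 | 0.306 | 0.277 | 0.82 |
| 0.7 | 0.241 | 0.229 | 0.90 |
| 0.9 | 0.142 | 0.140 | 0.97 |

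**Step 4: unequal variances.** With k the ratio of follow-up SD to baseline SD, the complete-pair variance ratio is k²(1 − ρ²)/(1 + k² − 2ρk). The slope of follow-up on baseline is ρk.
- k = 1.25: 0.78, 0.89 and 0.98 at ρ = 0.3, 0.5 and 0.7; exactly 1 at ρ = 0.8, where ρk = 1.
- k = 1.5: 0.87, 0.96 and 0.998 at ρ = 0.3, 0.5 and 0.7.

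**Step 5: how reliably the gain appears.** In 5,000 simulated trials at each ρ (39 complete pairs, equal variances), regression on baseline had the smaller SE in 99%, 95%, 85% and 51% of trials at ρ = 0.3, 0.5, 0.7 and 0.9.

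**The case against.** Group, time and their interaction with a participant effect is a standard and valid analysis of a randomised trial, and a condensed article may leave parameterisation to a fuller plan. That stands: nothing here is an error or a source of bias. But the article does state the model's terms, and as stated they leave baseline free in each arm.

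The gain depends on inputs nobody has seen. The trial excludes people already exercising moderately three or more times a week and progresses both arms towards the target, so a larger follow-up variance is plausible. Step 4 shows the gain could then be very small. This also stands and limits the claim.

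The adjustment relies on a baseline week unaffected by allocation. Allocation follows the baseline assessments and so does the monitoring week; the article does not say which of the two comes first. If allocation is disclosed first, a common-baseline constraint is unsupported and regression would adjust for a post-allocation measure. The planned change contrast would also be affected.

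Three stronger readings are tempting and not supported:
- A reader might take the complete-pair ratios as a gain worth 54%, 33% or 18% more participants (1/0.65, 1/0.75, 1/0.85). With the planned dropout the equivalents are 35%, 22% and 11% (1/0.74, 1/0.82, 1/0.90, from unrounded ratios), still assuming equal variances.
- A reader might infer that the trial is far below its stated power and that adjustment rescues it. That requires 0.6 to be a difference in SD units. The sample of 39 reproduces with 0.6 as f(V) and four time points, not as a two-group standardised difference, which needs 100 two-sided. How 0.6 should be read is a separate question; the variance ratios do not depend on it.
- A reader might infer that the group main effect will be tested, mixing in the pre-treatment week. The within-between sample-size method and the tertiary section's focus on change both point to the interaction.

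**Conclusion.** The point holds as an efficiency issue. As written, the natural primary contrast is a difference in change. It is valid under randomisation but less precise than a baseline-adjusted contrast whenever the slope of follow-up on baseline is not close to 1. At ρ of 0.3 to 0.7 with equal variances, the SE falls by about 14% to 5% with 60 at baseline and 39 at follow-up (SE ratios 0.86, 0.91 and 0.95), and by 19% to 8% in complete pairs. At ρ = 0.9, or with a clearly larger follow-up variance at moderate to high ρ, little or nothing is gained.

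These figures rest on an assumed ρ, the planned 35% dropout, the reading of group by time as the primary contrast, and a baseline week recorded before allocation is known. The equality with the change score is exact only for complete pairs.

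**What to change.** 1. Name the primary contrast as the CB-HB difference in percent achievement at post-intervention.
2. Estimate it by regressing follow-up percent achievement on group, baseline percent achievement and site, or by a mixed model with a common baseline mean (time, and group at post-intervention only). The two are similar but not identical, particularly with dropout, so choose one in advance.
3. Use the same form for the tertiary outcomes, and carry group, baseline value and site into the imputation model.
4. State that the baseline Actigraph week is completed before allocation is disclosed, if that is so. If it was not for some participants, do not impose the common baseline mean for them without a sensitivity analysis.

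The cost is a change of wording and a little extra analysis work, with no new data. The downside is reliance on the baseline week being pre-allocation. Enrolment began in September 2016, so this must be checked against actual practice.

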#### Centre-based exercise

A certified exercise physiologist will lead 60 min exercise sessions that include both aerobic, resistance, balance, and flexibility training at the centre once per week in a small group setting (3 to 5 participants), which is a frequency and duration often available in clinical and community exercise programs. Treadmill or Nustep will be the main aerobic training modalities during in-class sessions. Intensity will be monitored by heart rate and rating of perceived exertion (RPE, target: 12–15/20). Resistance training will target major muscle groups using exercise machines and hand-held weights as well as through functional activities. Exercise classes at the centre will be complemented by additional exercise to be performed independently at-home or in the community. The exercise physiologist will prescribe at-home exercise and collaborate with the participant to develop a plan for meeting the prescription. Participants will be encouraged to invite their care partner to attend this session. Participants will use an exercise diary to record their daily exercise.

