#### Home-based exercise

The HB program replicates an intervention used previously among middle to older aged adults, [28] except that care partners will be involved in the program planning. As with the at-home portion of the CB group, the exercise physiologist will prescribe exercises to be performed independently at-home or in the community and will develop a plan with the participant and care partner for meeting the prescription. The participant will mail in their exercise diary monthly. In addition, the exercise physiologist will talk to the participant and care partner each month by phone to discuss achievements and strategies to overcome recent barriers. Following the call, the exercise physiologist will adjust the exercise prescription and mail it to the participant with instructions to contact if there are any questions.

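### Site, the blocking factor, is a random effect with only two levels and does not sharpen the group x time contrast; clustering in the centre-based classes is a secondary, conditional concern

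*Protocol article*

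**What the plan says.** All references are to the protocol article.

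- **Design (Methods & design).** "The study will be conducted at two sites in Canada"; the Toronto site comprises two institutions. On allocation: "Participants will be randomly assigned to CB or HB after baseline assessments, blocked by site".
- **Primary model (Analysis, Primary objective).** A mixed-effects linear regression of percent achievement "as a function of group (CB, HB), time (baseline, follow-up and interim month 1, month 2 where relevant), and group x time". The random part is: "A random effect for participants and site (CB) will be included in the models".
- **Tertiary models (Analysis, Tertiary objective).** The same structure, but here "A random effect for participants and site will be included in the models", without the qualifier (CB). The article does not explain the qualifier.
- **Delivery.** Centre-based (CB) sessions take place "at the centre once per week in a small group setting (3 to 5 participants" (Centre-based exercise). The home-based (HB) programme is individual: "the exercise physiologist will talk to the participant and care partner each month by phone" (Home-based exercise).
- **Sample size.** 39 evaluable participants, raised to 60 for 35% dropout. No design effect or intraclass correlation is mentioned.

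**The concern.** A factor used to block the randomisation should normally be carried into the analysis in a form that removes its variation from the treatment contrast. Here it enters as a variance component to be estimated from two values. That component will often collapse to zero, and even when it does not, an intercept for site cannot explain differences between sites in *change*, which is what group x time measures. The stake is some lost precision in a trial planned on 39 evaluable people, and a risk of singular fits.

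The second issue concerns the same sentence. Group delivery in one arm only can make CB outcomes correlate within class. A model with participant and site terms alone treats CB participants within a site as independent. If they are not, the standard error of the contrast is too small.

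**Working it through.** **The plan's own figure.** 39 / (1 - 0.35) = 60, as stated. The 39 can be reached for the group x time test with effect size 0.6, alpha 0.05 and power 0.85 (how the article's beta of 0.85 is read here), for example with four measures and zero correlation between them. None of the inputs allows for site or class.

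**1. Site variance from two sites.** Assume the roughly 40 evaluable participants split equally, so n = 20 per site (the article gives no split). On a one-way ANOVA the variance estimate is zero when the F ratio on 1 and 38 df falls below 1:

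P(zero) = P( F(1,38) < 1 / [1 + n x ICC/(1 - ICC)] )

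| Site ICC (assumed) | Threshold | P(zero) |
|---|---|---|
| 0 | 1 | 0.676 |
| 0.05 | 1/(1 + 20 x 0.0526) = 0.487 | 0.511 |
| 0.10 | 1/(1 + 20 x 0.1111) = 0.310 | 0.419 |

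With all 60 participants observed, the figure at ICC 0.05 is 0.464. Counting the two Toronto institutions separately gives three levels and still 0.442 (N = 39, ICC 0.05). With 1 df, the 95% chi-square limits on the between-site mean square run from 0.2 to about 1018 times its estimate.

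**2. What this does to the contrast.** Write each participant's change as follow-up minus baseline. A site intercept is present at both times and subtracts out. In one simulated complete data set (40 people, two sites, two times, a 2-unit site shift), group x time was 0.2749 with SE 0.3588 both with and without the site intercept. Only a site x time term altered the SE.

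Now let site affect change. Take a residual SD of change of 1, a site SD of 0.3, 20 per arm and balance within site:

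- The true SE is about sqrt(2/20) = 0.316.
- The difference between the two sites has variance 2 x 0.09 = 0.18. Left unexplained, it adds on average 40 x 0.18/4 = 1.8 to the residual sum of squares, or 1.8/38 = 0.047 to the residual variance.
- The reported SE is then about 0.316 x sqrt(1.047) = 0.324.

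A simulation of change scores (20,000 runs) agrees: model SE 0.324 against empirical 0.315, type I error 0.042. With site as a fixed effect on change, the model SE is 0.316 and type I error 0.046. The reported SE is thus about 3% too large in this setting (0.324/0.315 = 1.03).

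**3. Class clustering in one arm.** Inputs: class size m of 3 to 5 (from the article), class ICC (assumed), 1:1 allocation, no clustering in HB.

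- Design effect in CB: DE = 1 + (m - 1) x ICC
- True SE / reported SE = sqrt((DE + 1)/2)
- Type I error = 2 x [1 - Phi(1.96/ratio)]

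| m | ICC | DE | SE ratio | Type I error |
|---|---|---|---|---|
| 3 | 0.01 | 1.02 | 1.005 | 0.051 |
| 4 | 0.05 | 1.15 | 1.037 | 0.059 |
| 4 | 0.10 | 1.30 | 1.072 | 0.068 |
| 5 | 0.10 | 1.40 | 1.095 | 0.074 |

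Simulation with classes of 3 to 4 and no site effect gives type I errors of 0.050, 0.057 and 0.064 at ICC 0, 0.05 and 0.10. A fixed site effect does not remove this (0.056 and 0.065 at ICC 0.05 and 0.10).

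**4. Cost of modelling the classes.** About 20 evaluable CB participants in classes of 4 make 5 classes, so 4 df; 20 in HB give 19 df. With equal variances, Satterthwaite gives (1 + 1)^2 / (1/4 + 1/19) = 4/0.3026 = 13.2 df, against 38 without clustering.

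**The case against.** **On site.** If a site intercept cancels from group x time, a zero variance estimate does that contrast no harm, so the 68/51/42% figures count an event rather than damage. That is correct. They show that the term is badly specified, and the only numerical cost found is mild conservatism when change differs by site. A reader might infer that the blocking factor is left out of the primary analysis, or that the estimate is biased. Neither is supported: site is named in the primary model, and balanced allocation within site protects the estimate. The qualifier (CB) may denote the delivery centre, since the Participants section uses the phrase CB site for the place people travel to, or it may mean a site effect in the CB arm only. The text does not settle it.

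**On classes.** A reader might infer that CB standard errors are too small as a matter of fact. That needs a within-class ICC above 0, and the article gives none. Several points weigh against a large one:

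- The follow-up activity monitor is worn in the week after the post-intervention assessment (Table 1), so shared class minutes are not what is measured.
- The class is one session a week, and the remaining exercise is independent.
- Class membership is not said to be fixed, and enrolment runs over two years.
- HB participants also share exercise physiologists, whose allocation is not described, so their independence is itself an assumption.

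All of this stands and keeps the class point conditional. It is also fair that a condensed article may leave a class term to the full plan. The site specification is different: the article states it outright, in two places and in two wordings.

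**Conclusion.** The site point holds in a limited form. A two-level random effect is a poor way to carry the blocking factor: its variance is practically not estimable, and the term does not help the contrast being tested. If change differs by site, the standard error is slightly too large (about 3% at an assumed site SD of 0.3 residual SDs of change). Type I error then falls a little below nominal, without bias. The unequal wording of the random effects in the primary and tertiary sections must be reconciled.

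The class point is real in structure but modest and conditional. For an assumed ICC of 0.01-0.10 and classes of 3 to 5, the true standard error is about 0.5-10% larger than reported and type I error is about 0.051-0.074. At ICC 0 there is no effect. It justifies a sensitivity analysis, not a change to the primary model.

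**What to change.** 1. **Site.** In the primary and tertiary models, replace the random site effect by a fixed site effect with site x time, keeping the participant random effect. Alternatively, use site as a covariate in a baseline-adjusted follow-up model. Name one of the two in advance. Cost: 1-2 degrees of freedom and a few words of analysis text.
2. **Wording.** State what (CB) after site means, say whether the Toronto institutions count as one site or two, and use the same description in both analysis sections.
3. **Classes.** Record class membership for each CB participant during delivery, when it is easy to capture. If classes prove stable, report a sensitivity analysis with a class effect in the CB arm only and small-sample degrees of freedom. The cost is more than a data field: with about 5 evaluable classes the class variance is itself poorly estimated, and effective degrees of freedom could fall to roughly 13. Intervals from that analysis will be noticeably wider, which is why it should support the primary analysis rather than replace it.
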